The study objectives are to determine the feasibility of performing a full-scale RCT for evaluating the effectiveness and safety of BHT for patients with chronic subjective tinnitus; to explore whether a TCM formula (BHT) has an additional effect on improving the impact of tinnitus in daily life and psychological function and also the perception of tinnitus after 8-week treatment and 4-week follow-up when compared to informative counseling alone; and to assess the safety of a TCM formula (BHT) in the patient population over the study duration of 12 weeks.

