## Methods

### Design Overview

This pilot study is a randomized, assessor blind, two-arm, parallel superior trial. The trial design was developed conforming to Standard Protocol Items: Recommendations for Interventional Trials (SPIRIT) Guidelines (Chan et al., 2013). The study will be conducted in the Integrative Medical Centre (IMC), CUHK, and the Chinese Medicine Specialty Clinic cum Clinical Teaching and Research Centre at School of Chinese Medicine, CUHK. A total of 24 patients will be recruited and allocated randomly to receive a TCM formula (BHT) and informative counseling or informative counseling alone. The oral BHT herbal granules will be taken twice per day continuously for 8 weeks. The measures of feasibility and potential clinical effectiveness will be collected at baseline, end of the treatment (week 8), and after the follow-up (week 12). This trial will be conducted in accordance with the Declaration of Helsinki and ICH Good Clinical Practice.

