#### Secondary Outcome Measures

A comprehensive set of outcome measures is employed to assess mainly the following six domains: tinnitus percept, impact of tinnitus, co-occurring complaints, quality of life, and treatment-related outcomes (Hall et al., 2016).1) Tinnitus Handicap Inventory in Chinese (Cantonese) version (THI-CH)

THI-CH is a 25-item self-administered questionnaire to quantify the impact of tinnitus on daily life. It has been demonstrated to be a reliable and valid measure of self-perceived tinnitus-related distress (Kam et al., 2009).2) Tinnitus functional index in Chinese (Cantonese) version (TFI-CH)

TFI-CH is a 25-item self-administered questionnaire that assesses eight domains of tinnitus impact: intrusiveness, sense of control, cognition, sleep, auditory, relaxation, quality of life, and emotion. It has been demonstrated to be a reliable and valid measure for intake assessment and treatment-related changes (Kam et al., 2018).3) Tinnitus sensation level

The tinnitus pitch and loudness matching will be measured according to Vernon and Meikle’s procedure (Vernon and Meikle, 2003).4) Self-rated visual analogue scale (VAS) on tinnitus loudness and annoyance (McCormack et al., 1988)

VAS is a validated and reliable tool for measuring subjective experience in tinnitus loudness and annoyance (Vernon and Meikle, 2003). It will be measured per ear. If a subject has bilateral tinnitus, the VAS will be measured differently for each side.5) Chinese (Cantonese) version of the Pittsburgh Sleep Quality Index (CPSQI)

The CPSQI is a self-rating questionnaire used to measure the quality and patterns of sleep in adults (Tsai et al., 2005).6) Chinese (Cantonese) version of Hospital Anxiety and Depression Scale (HADS)

The Chinese HADS is a 14-item questionnaire designed to assess the severity of mild, even sub-syndromal degrees of anxiety and depression (Leung et al., 1999).7) Adverse events

Adverse events will be recorded and coded to preferred terms as defined by the Medical Dictionary for Regulatory Activities (MedDRA), version 22.0.

All measurements will be taken at baseline, end of treatment (8 weeks after the first day of treatment), and after the 4-week follow-up. Kidney function will be examined before and after the treatment on those receiving BHT.

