#### Statistical Analysis

The primary feasibility outcomes will be reported descriptively with percentage, mean or median, standard deviation, or 95% confidence interval. As a pilot, the study is not powered to detect a statistically significant difference between groups. The treatment effect will be assessed with mean difference between two groups and confidence intervals of 75%, 85%, and 95%. A figure showing these CIs, minimum important difference, and the null value will help assess both statistical significance and the potential for clinical significance (Bell et al., 2018). All analyses will be conducted according to the intention-to-treat principle. Last observation carried forward will be used for imputing missing data because tinnitus is a chronic and constant symptom. Descriptive statistics will be computed for each of the analyzed variables. Exploratory inferential analysis will be performed using repeated-measures ANCOVA. Mean differences from baseline to end of treatment in each group will be examined by paired *t*-test or Wilcoxon signed rank test. Subgroup analysis on those with or without hearing loss, and those with unilateral or bilateral tinnitus will be made. All statistical tests will be two-sided, and *p* < 0.05 is considered statistically significant. The statistical software of SPSS 23.0 will be used for analysis.

Adverse events will be categorized and percentage of those experiencing some adverse events and serious adverse events will be documented. Chi-square tests will be performed to examine differences in the proportion of total and categories of adverse events within each group.

It is anticipated to find some preliminary evidence about the clinical effectiveness of BHT on chronic tinnitus, to identify if it is feasible to conduct a full-scale RCT of BHT and necessary changes to the protocol if possible. Statistical comparisons between groups may be misleading due to the many potential problems arising from small samples and low power. The results from statistical comparisons will be treated with great caution, and reported only with explicit reference to statistical power.

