#### Sample Size Estimation

As an exploratory pilot study, the stepped rules of thumb is used for estimating the pilot sample size (Whitehead et al., 2016; Bell et al., 2018). Although there is no previous study on BHT, we base the estimation of standardized effect size on two previous studies of compound TCM formula on chronic tinnitus (Lin et al., 2015; Chen et al., 2018). Using a mean difference estimate of eight and an estimate of standard deviation of 11–20 in similar populations, the standardized effect size is about 0.4 to 0.7. Assuming a reasonably medium (0.3–0.7) standardized effect size, a sample size of 10 per arm for the pilot is recommended for a 90% powered main trial. Therefore, a total of 24 patients will be needed in this trial, considering a 20% dropout rate.

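### The adverse-event chi-square tests are specified within arms, so they do not compare BHT with control, and chi-square would suit about 12 patients per arm poorly even if they did

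*Protocol article*

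**What the plan says.** All references are to the protocol article.

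- **Design Overview:** "This pilot study is a randomized, assessor blind, two-arm, parallel superior trial". The arms are BHT plus informative counseling and informative counseling alone.
- **Introduction (objectives):** one objective is "to assess the safety of a TCM formula (BHT) in the patient population over the study duration of 12 weeks".
- **Statistical Analysis, description of AEs:** "Adverse events will be categorized and percentage of those experiencing some adverse events and serious adverse events will be documented".
- **Statistical Analysis, test of AEs:** "Chi-square tests will be performed to examine differences in the proportion of total and categories of adverse events within each group". This is the only inferential plan for AEs. The section begins its general testing rule with "All statistical tests will be two-sided, and" and sets significance at p < 0.05. It also warns that between-group tests in a small pilot can mislead.
- **Sample Size Estimation:** "a sample size of 10 per arm for the pilot is recommended for a 90% powered main trial", and then "Therefore, a total of 24 patients will be needed in this trial, considering a 20% dropout rate".
- **Secondary Outcome Measures:** "Kidney function will be examined before and after the treatment on those receiving BHT". This sentence stands apart from the AE item in the list.

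**The concern.** In a two-arm randomised trial, the inferential question about AEs is whether they are more frequent with BHT than without it. A within-arm test cannot address that. Inside one arm, total events have no natural comparator. A chi-square across event categories would also treat overlapping categories in the same patients as independent observations.

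The phrase may be a slip for a between-group test. Changing that one word would leave a second weakness, because most AE categories in a trial of 24 patients will be too sparse for the chi-square approximation. An individual AE result could then be reported as significant, or not, according to which test was run. The results are meant to inform a full-scale RCT, so an AE signal or its absence may be carried forward.

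**Working it through.** **1. Inputs.** 10 per arm, 24 in total and 20% dropout (Sample Size Estimation); two arms (Design Overview); two-sided 0.05 (Statistical Analysis). The article states no allocation ratio and no expected AE rate. I assume 1:1 allocation and a common true event rate between 5% and 50%.

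**2. The plan's own figure.** 10 × 1.20 = 12 per arm, and 2 × 12 = 24, so the total reproduces. (Dividing by 0.80 instead gives 20/0.80 = 25 in total, a trivial difference.) The working size is 12 versus 12.

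**3. Expected counts.** If *m* of the 24 patients have the event, the expected cell counts are *m*/2 for event and (24 − *m*)/2 for no event in each arm. All are at least 5 only when 10 ≤ *m* ≤ 14, a pooled rate of 42% to 58%. With 10 completers per arm the condition needs exactly 10 of 20.

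**4. How often the condition fails, and what that does to the error rate.** Exact enumeration of all 12-versus-12 tables, same true rate in both arms, nominal 5%:

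| True event rate | P(some expected count < 5) | Pearson type I error | Fisher type I error |
|---|---|---|---|
| 5% | >99.9% | 0.2% | 0.02% |
| 10% | >99.9% | 1.5% | 0.25% |
| 20% | 98.7% | 3.9% | 1.2% |
| 30% | 84.8% | 4.9% | 1.7% |
| 40% | 51.1% | 5.9% | 2.1% |
| 50% | about 31% | 6.4% | 2.3% |

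The expected-count condition fails almost always for uncommon events. Pearson's error rate nevertheless exceeds 5% only at the 40% and 50% rates, and then by at most 1.4 points.

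**5. Tables where the choice of test decides the result.**

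- 4/12 versus 0/12. Pearson: 24 × (4×12 − 8×0)² / (12×12×4×20) = 24 × 2304 / 11520 = 4.8, p = 0.028. Fisher: 2 × C(12,4)/C(24,4) = 990/10626 = 0.093.
- 6/12 versus 1/12. Pearson: 24 × (6×11 − 6×1)² / (12×12×7×17) = 86400/17136 = 5.04, p = 0.025. Fisher: 2 × (924×12 + 792)/346104 = 23760/346104 = 0.069.

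Fisher's test first reaches significance at 5/12 versus 0/12 (p = 0.037) and at 7/12 versus 1/12 (p = 0.027).

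**6. Cost of the exact test.** At assumed rates of 30% versus 10%, Fisher's power at 12 per arm is 9.5% (Pearson 19.8%). At 50% versus 10% it is 42.5% (Pearson 60.0%).

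**The case against.** The strongest reply is that this is a slip of wording in a feasibility pilot. The sentence speaks of differences in proportions, which reads naturally as a comparison of arms. The article already asks for great caution with small-sample tests, and no AE result enters the feasibility thresholds. Much of this stands, and it limits the weight of the point. It does not remove the point: the caution names no exact method and leaves the 0.05 rule in place, and no other sentence states the between-arm comparison.

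Three stronger readings are tempting, and the documents do not support them.

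- **That the safety objective goes unanswered.** It does not. AE and serious AE percentages are planned, and the safety objective is not worded as a comparison. The comparison with counseling alone belongs to the effect objective.
- **That chi-square p-values would simply be wrong.** The expected-count condition is a rule of thumb, and the enumerated type I error is between 0.2% and 6.4%. The tables in step 5 were chosen because the tests disagree. The fault is a poor approximation in individual sparse tables, not gross error inflation.
- **That kidney testing in BHT patients only biases the AE comparison.** Nothing says that abnormal renal results will be recorded as AEs or enter the AE total. The asymmetry matters only if they are.

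It is also fair to say that Fisher's test is conservative, which for safety can hide a signal. That is a reason to lead with estimates and intervals, not a reason to keep the sentence as it stands.

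**Conclusion.** The point holds as a minor-to-moderate correction. As written, the only AE test does not compare the randomised arms. If a between-arm test was intended, chi-square is a poor choice at this size: some expected count is below 5 unless 10 to 14 of the 24 patients have the event, and plausible tables such as 4/12 versus 0/12 fall on opposite sides of 0.05 (0.028 against 0.093).

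The first part rests on the text alone. The second assumes 12 per arm, inferred from the sample-size section, and an uncorrected Pearson test. It bears mainly on individual AE categories. A total AE rate near one half could satisfy the expected-count condition.

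**What to change.** Replace the sentence on chi-square tests with the following:

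- By arm, the number and percentage of patients with at least one AE, at least one serious AE, and at least one event in each MedDRA category.
- The between-arm risk difference with an exact 95% CI.
- If a test is kept, Fisher's exact test between arms, labelled exploratory, with a statement that a non-significant result does not show safety.
- If abnormal kidney-function results are recorded as AEs, a separate table for them, outside the between-arm comparison, because only BHT patients are tested.

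The cost is a change of wording before analysis, with no new data and no more patients. The drawback is that Fisher's test is conservative and has low power here, so the counts and the interval should carry the message.

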#### Sample Size Estimation

As an exploratory pilot study, the stepped rules of thumb is used for estimating the pilot sample size (Whitehead et al., 2016; Bell et al., 2018). Although there is no previous study on BHT, we base the estimation of standardized effect size on two previous studies of compound TCM formula on chronic tinnitus (Lin et al., 2015; Chen et al., 2018). Using a mean difference estimate of eight and an estimate of standard deviation of 11–20 in similar populations, the standardized effect size is about 0.4 to 0.7. Assuming a reasonably medium (0.3–0.7) standardized effect size, a sample size of 10 per arm for the pilot is recommended for a 90% powered main trial. Therefore, a total of 24 patients will be needed in this trial, considering a 20% dropout rate.

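### The total of 24 does not cover the stated 20% dropout: it leaves an expected 9.6 per arm, not 10, and holds only up to 16.7% dropout

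*Protocol article*

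**What the plan says.** The section Sample Size Estimation sizes the pilot by a published rule: "the stepped rules of thumb is used for estimating the pilot sample size". It expects a mean difference of 8 with a standard deviation of 11 to 20, adopts a medium effect band of 0.3 to 0.7, and states that "a sample size of 10 per arm for the pilot is recommended for a 90% powered main trial". The last step is the dropout allowance: "Therefore, a total of 24 patients will be needed in this trial, considering a 20% dropout rate".

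The section Statistical Analysis adds that "As a pilot, the study is not powered to detect a statistically significant difference between groups". It also plans intention-to-treat analysis with last observation carried forward.

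**The concern.** A dropout allowance exists so that the target number is still there after the expected losses. Here the target is 10 per arm and the expected loss is 20%, yet 80% of 24 is fewer than 20. The figure comes from increasing the target by 20% instead of dividing it by the retained fraction.

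At stake is whether the justification for the number of patients is true as written. The Discussion says that the effect estimates will inform planning of the full-scale trial, so the number of patients with observed outcomes has some bearing on that use. The allowance is only 2 patients per arm, so an error of 1 patient per arm is half of it.

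**Working it through.** **Inputs, all from Sample Size Estimation:** target 10 per arm (20 in total); dropout d = 0.20; stated total 24. Equal allocation (12 per arm) is assumed, because the target is given as one number per arm and the article states no ratio.

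**1. Reproducing the plan's figure.** Target x (1 + d) = 20 x 1.20 = 24. This matches exactly.

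**2. What 24 leaves at 20% dropout.** 24 x 0.80 = 19.2 in total; 12 x 0.80 = 9.6 per arm. The expected shortfall is 0.4 patients per arm, 0.8 in total.

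**3. What 20% dropout requires.** Target / (1 - d):
- in total, 20/0.80 = 25;
- per arm, 10/0.80 = 12.5, rounded up to 13, so 26 with equal arms.

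The plan is 1 to 2 patients short.

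**4. What dropout 24 does cover.** 1 - 10/12 = 1 - 20/24 = 0.167, so 16.7%, or 2 patients per arm.

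**5. Chance of keeping the target at 20% dropout.** Assume independent dropout with probability 0.2 in both arms. For one arm of 12:

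P(X ≥ 10) = 66 x 0.8^10 x 0.2^2 + 12 x 0.8^11 x 0.2 + 0.8^12 = 0.283 + 0.206 + 0.069 = 0.558.

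Both arms: 0.558^2 = 0.312. At least 20 of 24 overall, regardless of arm: 0.460.

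For scale, 13 per arm gives P(X ≥ 10) = 286 x 0.8^10 x 0.2^3 + 78 x 0.8^11 x 0.2^2 + 13 x 0.8^12 x 0.2 + 0.8^13 = 0.246 + 0.268 + 0.179 + 0.055 = 0.747, and 0.747^2 = 0.558 for both arms. Correct inflation protects the expected number; it is not a guarantee.

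**6. Effect on precision of the standard deviation.** The approximate relative standard error of a pooled standard deviation is 1/√(2 df). With 20 completers (18 df) it is 1/√36 = 16.7%. With 19.2 (17.2 df) it is 1/√34.4 = 17.0%.

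**7. Effect range.** 8/20 = 0.40 and 8/11 = 0.73. The plan's "the standardized effect size is about 0.4 to 0.7" is fair rounding.

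**8. Side check on the 90% label, under an assumed criterion.** The article does not show the rule's table. As a rough check, choose the pilot size m per arm that minimises m + n, where n = 2q²/δ², δ is the standardised effect, and q is the 90% quantile of a non-central t with 2m - 2 df and non-centrality 1.96. At effects 0.3, 0.4, 0.5 and 0.7 the best m is 19, 15, 12 and 9. If the non-centrality uses the main trial's t critical value and n is rounded up to whole patients, it becomes 17, 14, 10 and 8. The criterion is almost flat: at 0.3, m = 10 gives 279.8 per arm (pilot plus main) against 269.9 at best, 3.7% more; at 0.4, 161.8 against 159.1, 1.7% more.

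**The case against.** **The gap is negligible.** It is 0.4 of a patient per arm in expectation, and 10 is a rule of thumb, not a threshold at which something fails. This stands as to consequence: the precision of the standard deviation barely moves. It does not make the sentence correct, since the stated total does not deliver the stated target at the stated dropout.

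**The primary outcomes do not need 10 completers per arm.** This stands. Both completion rates use all recruited patients as denominator, and the recruitment rate uses those approached. With 24 recruited, the data completion criterion of at least 80% needs 20 completers (20/24 = 83.3%; 19/24 = 79.2%). A pilot that passes therefore keeps 20 in total, though not necessarily 10 in each arm.

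**All 24 are analysed under intention to treat with carried-forward values.** True, but a carried-forward value adds no new outcome observation, and the plan's own allowance counts dropouts as lost.

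**Stronger readings that the document does not support.**
- A reader might infer that 10 per arm was meant to give the pilot 90% power. The 90% belongs to the future main trial, and the pilot is expressly not powered.
- A reader might infer from step 8 that 10 is the wrong number for a 90% powered main trial, or that the label should read 80%. The criterion is assumed, its answer shifts with the calculation details, and the loss from using 10 is small. A stepped rule gives one number for a whole band, so variation within the band does not contradict it. Only the cited table can settle the point. Relabelling to 80% would not fit either: the same check at 80% power and effect 0.3 gives 11 to 14, not 10.
- A reader might object that 0.73 lies outside the 0.3 to 0.7 band. The plan writes an approximate 0.7, and that is no error.

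**Conclusion.** The dropout statement is wrong as written. The total of 24 comes from multiplying by 1.2 where dividing by 0.8 was needed. At 20% dropout it leaves an expected 9.6 per arm, it covers losses only up to 16.7%, and it is 1 to 2 patients short of what 20% would require.

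These figures need only the sample size section, plus equal arms for the per-arm numbers. The probability of about 0.31 that both arms keep 10 further assumes independent dropout at the same rate in each arm. The practical effect is minor and does not undermine the pilot's feasibility aims.

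The effect range stands, and the 90% label is neither confirmed nor refuted by the article.

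**What to change.** Keep 24 patients and restate the allowance in Sample Size Estimation, for example:

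> 24 patients (12 per arm) leave 10 evaluable per arm if dropout does not exceed 16.7% (2 per arm); at 20% dropout about 9.6 per arm are expected.

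This is a change of text only, with no extra patients and no change to the analysis. Its cost is a slightly less favourable stated allowance. If the sponsor prefers to keep the 20% figure with 10 per arm, the total has to be 25, or 26 with equal arms.

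As an optional check, the sponsor can confirm against the cited rule's table that 10 per arm is its step for a 90% powered main trial in the 0.3 to 0.7 band. No change to that label or to the effect range is requested on the present evidence.

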### Study Monitoring and Quality Assurance

The study will be undertaken in accordance with this clinical trial protocol, ICH guidelines for Good Clinical Practice, the Declaration of Helsinki, and the applicable regulatory requirements of Hong Kong. Case report forms (CRFs) will be developed for recording the individual patient data. The investigators will assure that all reported trial data are accurate, complete, and verifiable from source documents. Work manual and training workshop will be provided to all involved research staff.

The study committee will hold regular conferences to monitor the patients’ safety and the integrity of the data with respect to the original study design, and to provide advice on study conduct. Authorized representatives of the ethics committee may visit the research clinic to perform inspections.

## Discussion

Although various Chinese herbal medicine formulae have been used to treat tinnitus in East Asia, none of them was supported by sound clinical evidence. We aim to establish a robust evidence for the clinical application of CHM formulae for chronic tinnitus. This pilot study is the first step to explore the feasibility and scientificity of a further full-scale RCT. Its expected results will help us decide on the appropriate approaches to find potential participants, the inclusion criteria, and efficient ways to manage the study and reduce the withdrawal rate. The results on the estimations of study effects will be used as a reference for deciding on the planning of a further full-scale RCT.

According to Chinese medicine theory, the pathogenesis of chronic subjective tinnitus is mainly the insufficiency of essence to maintain the normal function of kidney and stagnation of Qi and blood flowing in the meridian through ear. A literature review on the clinical studies of Chinese herbal medicines for tinnitus from 2003 to 2013 has found that the most common syndromes are insufficiency of kidney essence and stagnation of Qi and blood flowing (Qiu et al., 2015). Thus, the general treatment principle for chronic subjective tinnitus is to tonify the essence of kidney, promote blood flowing, and dredge the meridian passage around ears, Bushen Huoxue Tongluo in Chinese. The CHM formulae with such effects are widely used to treat chronic tinnitus. Studies have shown that they could effectively reduce pathological damage to the primary auditory cortex (Wang et al., 2017), improve the microcirculation of the inner ear and have a sedation effect (Zhong et al., 2001; Zheng 2006), and inhibit 5-HT (hydroxytryptamine)/Rho-associated kinase signaling pathway (Zhou et al., 2015).

Er Long Zuo Ci Pill (耳聾左慈丸 in Chinese), a traditionally well-known formula, is widely used to treat tinnitus and deafness in China. It was found to be one of the most often used formulae to treat tinnitus in the recent 30 years (Zhang et al., 2015). Some clinical trial studies have reported that Er Long Zuo Ci Pill could reduce the tinnitus loudness and hearing threshold and relieve the associated symptoms (Zhang et al., 2015; Zhang, 2017). Mechanism studies have indicated that Er Long Zuo Ci Pill could protect the cochlear hair cells from gentamicin-induced ototoxicity (Dong et al., 2010); decrease auditory brainstem response threshold; inhibit the expression of tumor necrosis factor alpha, interleukin-6, and interleukin-1 beta (Li and Wang, 2015); upregulate protein expression of aquaporin-4 in cochlear tissues (Lv et al., 2015); and reduce spontaneous discharge of external cortex of inferior colliculus and secondary auditory cortex induced by salicylic acid (Wang et al., 2009).

Er Long Zuo Ci Pill is composed of eight herbs, namely, *Rehmannia glutinosa* (Gaertn.) DC (Orobanchaceae) (Dihuang), Cornus officinalis Siebold & Zucc (Cornaceae) (Shanzhuyu), Paeonia × suffruticosa Andrews (Paeoniaceae) (Mudanpi), Bupleurum falcatum L (Apiaceae) (Chaihu), Poria cocos (Schw.) Wolf (Fuling), Magnetitum (Cishi), *Dioscorea oppositifolia* L (Dioscoreaceae) (Shanyao), and Alisma plantago-aquatica subsp. orientale (Sam.) Sam (Alismataceae) (Zexie), which has the main effect of tonifying kidney essence. To enhance its treatment effect on chronic tinnitus, some formulae modified from Er Long Zuo Ci Pill have been studied in clinical trials. It has been demonstrated that its clinical effect on tinnitus could be augmented by combining herbs with an effect of activating blood circulation (Xie et al., 2016).

Following the treatment principle, we further combine Er Long Zuo Ci Pill with several other herbs with an effect of activating blood circulation, dredging the meridians, and tranquilizing the mind to make the formula BHT. In BHT, *Rehmannia glutinosa* (Gaertn.) DC (Orobanchaceae] (Dihuang), Cornus officinalis Siebold & Zucc (Cornaceae) (Shanzhuyu), and Dipsacus asper Wall. ex DC (Caprifoliaceae) (Xuduan) have the effect of tonifying kidney essence. Paeonia × suffruticosa Andrews (Paeoniaceae) (Mudanpi), Salvia miltiorrhiza Bunge (Lamiaceae) (Danshen), Conioselinum anthriscoides “Chuanxiong” (Apiaceae) (Chuanxiong), and Prunus persica (L.) Batsch (Rosaceae) (Taoren) have the effect of activating blood circulation. Poria cocos (Schw.) Wolf (Fuling), Bupleurum falcatum L (Apiaceae) (Chaihu), Pinellia ternata (Thunb.) Makino (Araceae) (Fabanxia), Pueraria *montana* var. lobata (Willd.) Maesen & S.M.Almeida ex Sanjappa & Predeep (Fabaceae) (Gegen), and Acorus calamus var. angustatus Besser (Acoraceae) (Shichangpu) have the effect of dredging the meridians. Ziziphus jujuba Mill (Rhamnaceae) (Suanzaoren), Magnetitum (Cishi), and Margaritifera Concha (Zhenzhumu) have the effect of suppressing hyperactive liver yang and tranquilizing the mind.

BHT is developed for those with the most common TCM syndrome, kidney essence deficiency, and stagnation of Qi and blood flowing in the meridian around the ears, in patients with chronic tinnitus. From the view of TCM, BHT is of generally neutral nature (not hot or cold), which enlarges the scope of its clinical application. During the study, the clinical symptoms and signs, pulse, and tongue diagnosis will be collected. Further analysis of its effects on those patients with TCM diagnosis of cold, warm, or cold–heat complication will be made.

The study results will provide an estimation of the general add-on treatment effect of CHM on chronic tinnitus. The choice of informative counseling alone as control will help to control some non-specific treatment effects, such as natural history and regression to the mean; however, it should be noted that the placebo effect could not be ruled out from the comparison results. The possible placebo effect of CHM may have effects on the outcomes, especially subjective ones. A placebo-control and some objective outcomes, such as functional near-infrared neuroimaging (fNIR), may be employed in the design of future full-scale RCT.

